## Abstract

Eating disorders (EDs) present a chronic issue to child paediatric mental health services due to their high mortality and relapse rates. The transition from Child and Adolescent Mental Health Services to Adult Mental Health Services is a particularly high‐risk period for young people with EDs given their high vulnerability to change, which can negatively impact treatment outcomes. However, there is lack of evidence on the feasibility of inclusive and youth‐specific interventions that address the multiple and complex needs of this group during their transition to adult care. This proposed study aims to develop a newly introduced model of care called Transition for Eating Disorder Youth intervention (TEDYi) for young people aged 16–18 years with EDs transitioning from adolescent ED services to adult care. TEDYi will be co‐produced with young people, carers, and staff targeting interpersonal and psychosocial needs during the transition process. The first phase of the study involves interviews with young people (*N* = 15) and carers (*N* = 15) as well as focus groups with mental health professionals (*N* = 15) across four ED adolescent and adult specialist services to explore their transition experiences. The second phase, consists of four Experience‐Based Co‐Design workshops, aimed at collaboratively developing and refining TEDYi.

## INTRODUCTION

1

Eating disorders present a significant public health concern and pose a chronic issue to child paediatric mental health services due to their high mortality and relapse prevalence (Walker & Lloyd, 2011). Eating disorders are life‐threatening diseases which can result in premature death among young adults, with the highest mortality rate among all psychiatric disorders and they are linked to poor psychosocial outcomes, mental health comorbidities and repeated hospital admissions (Berends et al., 2018; Cardi et al., 2017; Treasure et al., 2011). An estimated one‐third of all deaths in young people with anorexia are due to cardiovascular issues, and 25% of this population have attempted suicide. Anorexia (AN) and bulimia nervosa (BN) are the most prevalent types of EDs among young people, and they exhibit alarming symptoms ranging from starvation to purging and using laxatives to excessive exercising. Eating disorders typically first appear in adolescence and early adulthood (Arcelus et al., 2008) where two thirds of cases continue for 9 years and a third for over 20 years (Eddy et al., 2017).

Young people often present to Child and Adolescent Mental Health Services (CAMHS) with overlapping symptomatology of AN and BN due to the diagnosis complexity underlying EDs. A study found that the mean age for young people presenting in CAMHS is 14.6 years and only 27.7% are transitioned to adult services (Arcelus et al., 2008). However, a considerable proportion is not accepted by adult specialist services and might be seen by generic services or treated in primary care, which is worrying due to lack of staff training and skills around EDs (Winston et al., 2023). Studies show that young people with EDs are more likely to experience poor transitions due to lack of continuity of quality care and fragmented social support in the community (Bryan et al., 2022). Young people experiencing poorly managed transitions which do not promote graded and flexible pathways are less likely to take ownership of their condition and, therefore become more prone to poor mental health outcomes (NHS, 2019). A large‐scale national survey identified substantial barriers to ED transitions, including the absence of personalised transition plans and limited involvement of carers. Additionally, the survey highlighted a therapeutic disconnect between child and adult care plans, as adult services often lacked a developmental approach to treatment (Winston et al., 2023).

The Royal College of Psychiatrists (2022) and NHS England (2015) advocate for prioritising ED transitions and improving discharge support, aiming to reduce relapse, optimise self‐efficacy, and enhance quality of life for young people. The transition from CAMHS to adult services is a particularly high‐risk period for young people with EDs due to their vulnerability to change, which has been identified as a significant risk factor for relapse and poor treatment outcomes. In fact, anorexia was initially conceptualised as a response to change stemming from overwhelming emotions (Bruch, 2001). Young people with EDs during emerging adulthood are likely to experience additional transitions pertinent to residential, occupational, and developmental changes, identity reconstruction, change in therapeutic models from CAMHS to AEDS, which often increase the risk for social isolation (Webb & Schmidt, 2021). Due to the high mortality rates and associated physical health complications, well‐planned transitions in individuals with EDs are pressing. Optimal transitional care with developmentally appropriate interventions has the potential to improve prognosis, increase engagement and provide ongoing support (Wales et al., 2021). Experience evidence‐based interventions can empower young people as well as their families, and those involved in service delivery by facilitating understanding of their roles and increasing self‐management of symptoms. Previous research highlights that guided self‐help interventions lead to poor outcomes underlined by low participation and high dropout rates and, therefore personalised guidance can enhance motivation and engagement (Giel et al., 2021). The debilitating effects of anorexia and BN are linked to family dependency and poor psychosocial functioning in the community.

The commissioning framework for ED services in England acknowledges the importance of including individuals with EDs in the development and implementation of care approaches and interventions. However, initiatives for young people specifically with EDs co‐producing care approaches and interventions are currently lacking (Lewis & Foye, 2021). Co‐production is a form of patient and public involvement (PPI) that is widely used in health research (Hayes, et al., 2012), where service users, family members, carers, and service providers collaborate to improve their own care and service provision (Norton, 2019). Experts by experience can identify needs, care gaps, meaningful outcomes, ultimately increasing transparency and improving care (Madden et al., 2020). A recent report published by the Beat Eating Disorders charity (2020) voicing the lived experiences of people with EDs and their carers, echoes the infrastructural barriers to transitions and the lack of a standardised transition plan with 50% describing the process as either “extremely poor” or “poor”. The lack of effective communication coupled with abrupt transitions prompted recommendations for further family involvement to prevent exacerbation of ED behaviours.

There is very little evidence about the feasibility and effectiveness of inclusive and youth‐specific interventions that address the complex needs of this group as they transition to the community to avoid preventable death causes. Therefore, this study aims to develop a series of empowering workshops to create the *Transitions for Eating Disorder Youth intervention* (TEDYi) to support young people aged 16–18 years with AN and/or BN, and other comorbid mental health problems, and their families as they transition to adult care. This approach aims to reduce anxiety and increase self‐efficacy (symptom self‐management) by building on existing skills and promoting hope. Evidence‐based research in this area is considerably lacking and we need interventions targeting transition preparations of young people moving to adult services at least 6 months before discharge (Arcelus et al., 2008). TEDYi will be person‐centred and co‐produced with young people (who have moved to adult services or are approaching 18 years and are due to transition from adolescent ED specialist services), carers and staff (nurses, nutritionists, family therapists, psychologists, psychiatrists, occupational therapists, GPs) with lived ED transition experience targeting interpersonal and psychosocial needs during the transition process.

The intervention will be developed collaboratively with young people, carers, and mental health professionals, integrating their contributions during the co‐production phase. We have outlined a preliminary intervention plan guided by the literature and previous evidence‐based supplementary interventions designed for adults. However, we aim to receive feedback on this proposed framework and make necessary adjustments and modifications, based on the perspectives, and lived experiences of the involved stakeholders. This process ensures that TEDYi is aligned with the needs of the target population. We aim to determine the frequency, mode of delivery and training materials included in the intervention based on previously conducted Experience‐Based Co‐Design (EBCD) workshops. Experience‐Based Co‐Design enables service users, families, and staff to work collaboratively, using the participants' lived experience, to co‐produce service design and contribute to research development. Experience‐Based Co‐Design has been implemented successfully in breast and lung cancer patients across two London teaching hospitals (Tsianakas et al., 2010) and in diabetic ED patients (Zaremba et al., 2022). We aim to co‐produce training materials for TEDYi including a handbook guiding the workshops and an accompanying animated video showcasing interactions of young people with peers and carers who have experienced transition. Young people will prepare for transition 3–6 months before discharge between services. This preparation aims to prevent relapse and manage the coexistence of physical and mental health symptoms.

## THEORETICAL FRAMEWORK

2

Transition for Eating Disorder Youth intervention will be informed by previously effective intervention transition models‐ECHOMANTRA and TRIANGLE‐ for adult patients with EDs. ECHOMANTRA is a skills‐training intervention for patients and carers aimed to sustain recovery after discharge based on the interpersonal cognitive model (Treasure & Schmidt, 2013) which proposes that improving patient and carer communication will lead to better transition outcomes (Adamson et al., 2019). ECHOMANTRA includes coping strategies, for recovered ED patients, towards reconstructing an identity that is not emanated from the ED. Previous research has found that individuals with AN are particularly vulnerable to family members' expressed emotions (overprotection and criticism), due to excessive worry and anxiety (Rienecke, 2018). Research shows that add‐on interventions such as ECHOMANTRA facilitates psychosocial functioning and improves outcomes for people with EDs and their carers (Cardi et al., 2017). Thus, the aim is to equip carers with skills that will foster positive emotional responses in young people with EDs. Furthermore, it is well‐established in the extant literature that carers are often excluded from adult care‐plans (Eisler et al., 2022), both due to confidentiality and expectations that individuals are well‐skilled to manage an independent lifestyle once they have transitioned. However, young people previously hospitalised in highly supportive settings transferred to adult care and/or community settings which follow a more independent care model, often lack life‐skills, and encounter major challenges in leading an adult‐like lifestyle (Webb & Schmidt, 2021). Research evidence suggests that carer involvement in young people's care journey has the potential to reduce loneliness, and social isolation by empowering the young person (Cardi et al., 2017). Thus, carers will be included in the co‐production plan to reflect on their lived experiences of transition and voice their needs. Mental health professionals will also be included to facilitate the transition process, specifically, the *letting go* period for the young person. Young people often build strong attachments to keyworkers in services and ending therapeutic relationships may be a triggering factor for relapsing during transitions.

Similarly, TEDYi will be developed in line with TRIANGLE's and ECHOMANTRA’S underlying aims of upskilling young people, carers, and mental health professionals during transition periods. TEDYi aims to use a similar format around graduate leave planning although in‐person workshops will be aimed to be delivered by a peer‐mentor. Drawing upon discussions and reflective dialogs with mental health practitioners, clinical academics, and individuals with lived experiences of EDs, alongside prior evidence‐based interventions, we have outlined the foundational principles guiding TEDYi. However, our objective is to elicit specific feedback on the proposed structure and delivery approach through the present co‐production and development phase involving young people, carers, and mental health professionals from adolescent and AEDS. Carers and adults with EDs valued ECHOMANTRA in terms of psychosocial skills gained and maintaining a recovery identity and they emphasised the need for more consistent follow‐ups post‐discharge. Therefore, TEDYi aims to include a peer‐support mentor with lived experience to run preparation transition workshops. The proposed intervention will focus on building hope, deconstructing a non‐ED identity, managing emotional responses to change, and encouraging service engagement and follow‐ups, restructuring mealtime and planning, involving a primary carer. In the long run, TEDYi seeks to comprehensively address the interpersonal, psychosocial, and emotional needs of both young people and carers throughout the transition process.

## AIMS AND OBJECTIVES

3

In the present study we aim to:conduct interviews with young people and carers who will or have moved from adolescent ED units to adult services and the community within the last 5 years;conduct focus groups with mental health professionals (staff) with lived service transition experience, to explore their views and roles in the transition process;receive feedback on foundational TEDYi outline and implement suggested adjustments.co‐design TEDYi and develop, together with young people, carers, and mental health professionals (staff), the format, structure and materials included in the intervention based on EBCD workshops;explore recommendations for transitional care from young people, carers, and mental health professionals.

## RESEARCH QUESTIONS

4

What are the views and perspectives of young people, carers, and mental health professionals about transitioning from adolescent ED services to adult care?What are the personal reflections of young people, carers, and mental health professionals on the proposed content and structure of TEDYi?What changes do young people, carers and mental health professionals recommend to TEDYi structure, format, and delivery?How can TEDYi be improved based on personal lived experiences of young people, carers, and mental health professionals?How can carers be involved in transition preparation and planning?What factors should TEDYi entail for successful and sustainable implementation in adolescent services long‐term?What strategies can be employed to improve joint working between adolescent services and adult services and facilitate the promotion of TEDYi?What strategies can we implement to maintain engagement, participation and adherence in young people, carers, and mental health professionals?What measures can be put in place to provide optimal support to both carers and mental health professionals during the transition process?

## METHODS

5

### Study design

5.1

This study will use qualitative methodology to explore the complexity of transitions from adolescent to adult ED services. Qualitative methodology will provide a deeper understanding of young people's and carers' lived experiences which would not be encapsulated in quantitative research. The present study includes two phases: (a) interviews and focus groups, and (b) EBCD workshops. Young people who wish to be part of the wider co‐production group will be invited to the four follow‐up EBCD workshops. Focus groups will be used with mental health professionals as they are more familiar with sharing sensitive content in groups due to their profession (Patel et al., 2016). Interviews will be conducted with young people and carers to allow individual expression and avoid feelings of fear that may arise during sharing lived experiences in larger groups. The interviews will be recorded for use in EBCD workshops. Interviews and the four EBCD workshops will help the research team understand the priorities of young people and carers during the transition process and to address specific themes of concern.

### 1^st^ phase interviews and focus groups

5.2

Four postgraduate research assistants, a Doctorate Clinical Psychology trainee and a doctoral researcher with lived experience will conduct the interviews and focus groups. All students have received qualitative training and have relevant clinical experience. All interviews will take place in the service the young people attend or online via Microsoft Teams depending on availability and personal preference. The interviews will include young people (*N* = 15) and carers (*N* = 15). All interviews will last 30–60 min. For the focus groups, we aim to recruit mental health professionals (*N* = 15) from adolescent and adult services and primary care (GPs). They will be separated into two focus groups both including mental health professionals across adolescent and adult services. All interviews and focus groups will be conducted by one moderator and a research assistant to observe, take field notes, and record any non‐verbal cues. The focus groups will last 60–90 min. Participants will receive a payment of £10 Amazon Vouchers for their participation in interviews. The participant information leaflet of the study and the researcher clearly state that if the participants choose to be audio or video‐recorded, we may use some of their quotes or video‐recorded material to create a short video that will be discussed during the subsequent workshop phase. To ensure confidentiality and protect participant anonymity, blurring faces will be used and no participant will be identified through the shared recorded materials. In case, participants do not wish to share any specific or sensitive information in the follow‐up phase, they will let the researcher know. However, recording interviews on both audio and video and potentially showing parts of these recordings in subsequent workshops could introduce concerns about participant bias and willingness to disclose sensitive information. To mitigate this risk, the research team will aim to create a trusting, inclusive and safe environment during the interview phase to encourage open and honest sharing of lived experiences. Researchers are well‐trained in reflexive qualitative approaches and have their own lived experiences which will empower the interview process. After the recording participants will have the opportunity to provide feedback or ask questions about the process to address any concerns they might have and reinforce the confidentiality measures. An independent reviewer of the team will contribute actively to the selection of recorded segments to be shown in the workshops.

The following predetermined codes will be used as prompts in interviews and focus groups: experience with services, current or past support throughout the transition process, barriers and facilitators in the transition process, continuity of care, effective communication, the role of staff in the process, recommendations for mechanisms in place, next steps. In the focus groups with the mental health professionals, we will also focus on the following: approaches to teamwork and decision‐making within and across services, resources to facilitate transition and continuity, role development, skills and training necessary to improve staff confidence in the provision of effective transition and continuity to users and carers. These codes were developed as a continuous process of collaboration between the team members, after a literature search and input from PPI members.

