### Recruitment and sampling technique

5.5

Local collaborators across four NHS Trusts and ED units will facilitate recruitment by identifying eligible young people who are close to 18 years and will be moving to adult services within the next year from the starting date of the study and/or young people who have recently transitioned to adult services or are attending an outpatient community team. The same process will be applied for eligible carers. During weekly community meetings and adverts on boards, the collaborators will invite young people to participate in the study. Young people and carers attending adult outpatient services will be contacted through post/phone by their responsible clinician. Additionally, the study will be advertised by local collaborators through leaflets/posters in ED specialist services. Young people will contact their responsible clinician if they want to participate, who will then inform the research team. In some cases, young people and their carers may be initially contacted by an invitation letter signed by their care coordinator/clinician. A follow‐up phone call/email will be made by CAMHS or Adult Mental Health Services personnel if they do not respond to the original invitation. Purposive sampling will be used to identify eligible young people, and convenience sampling for carers and mental health professionals. The sample will be proportionally stratified to represent diverse demographic characteristics if more than 15 participants are identified in each group. The sample size was decided based on information power allowing for sufficient information, diverse experiences, and new knowledge, as well as previous studies conducted with qualitative design and estimated number of eligible participants after consultation with local collaborators. Accordingly, our targeted population is expected to share sufficient information about transition experiences and will provide new knowledge for analysis. See Figure 1 for recruitment and study procedures.

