### Consent

5.8

The young person/carer/mental health professional will be required to provide consent to participate in the interviews/focus groups, for the interviews/focus groups to be recorded, and for the four follow‐up workshops. At each phase of the study, the researchers will ensure that participants have a good understanding of the risks and benefits of participating, what is expected of them, their right to withdraw during or after 4 weeks of data collection and how their data will be used to inform the proposed intervention. Ethical approval has been obtained by the UK Health Departments' Research Ethics Service (NHS RECs), London ‐ Westminster Research Ethics Committee, using the Integrated Research Application System.

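### Agreeing to the recording that the analysis needs also opens it to possible use in the workshop film, and face blurring, the only masking step named, cannot reliably deliver the promise that no participant will be identified

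*Protocol article*

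**What the plan says.** All places are in the protocol article.

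- **Section 5.1, Study design:** "The interviews will be recorded for use in EBCD workshops". No condition is attached.
- **Section 5.2, 1st phase interviews and focus groups:** the leaflet and the researcher tell participants that "if the participants choose to be audio or video‐recorded, we may use some of their quotes" or video material in a short film for the workshops. On anonymity, "blurring faces will be used and no participant will be identified through the shared recorded materials". Participants who want specific or sensitive information kept out of the next phase are to tell the researcher. The section acknowledges that recording, and showing parts of it, may affect what people are willing to disclose. It answers with an atmosphere of trust, a chance to raise concerns after the recording, and an independent team member who helps to choose segments.
- **Section 5.3, 2nd phase workshops:** the film lasts 20 minutes. Its content is reviewed with patient and public feedback, and material judged too sensitive is left out.
- **Section 5.7, Data analysis:** interview recordings are transcribed verbatim, and coding works from the transcripts.
- **Section 5.8, Consent:** each person "will be required to provide consent to participate in the interviews/focus groups, for the interviews/focus groups to be recorded", and for the workshops. The section also mentions "their right to withdraw during or after 4 weeks of data collection".

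**The concern.** One act of agreement serves two purposes that differ in risk. Recording for transcription keeps the material within the research team. Use in the film shows it to other young people, carers and clinical staff. Section 5.8 lists consents for participation, recording and the workshops, but none for showing footage to others.

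The anonymity statement is absolute, while the only technique offered for achieving it acts on the picture. A first-person account of moving between eating disorder services can be recognisable from the voice or the events described.

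Two things are at stake. The first is confidentiality, for participants as young as 16. The second is candour on the first research question: the interview prompts cover experience with services, barriers and the role of staff, and professionals are among the viewers.

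**Working it through.** No sample size, power or error rate bears on this point, so the check is textual, with one count.

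**1. Is recording optional?** Section 5.2 says "if the participants choose to be audio or video" recorded, which is a choice. Section 5.1 says the interviews will be recorded and gives the workshops as the purpose. Section 5.7 describes analysis from interview recordings only. Field notes are taken at every session (5.2), but 5.7 does not say how an interview without a recording would be analysed. The tension is therefore 5.1 and 5.7 against 5.2.

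**2. Does recording carry film use?** Under 5.2, possible film use follows from the choice to be recorded. The stated way to limit it is for the participant to tell the researcher what must not be shared. That is an opt-out which the participant must start, and it is framed around particular content. No section describes agreeing to recording for analysis alone.

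**3. Which safeguards hide identity?**

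| Safeguard | Section | Acts on |
|---|---|---|
| Face blurring | 5.2 | Identity (picture only) |
| Participant's objection | 5.2 | Content |
| Discussion after recording | 5.2 | Participant's concerns |
| Independent segment reviewer | 5.2 | Content |
| Patient and public feedback on the film | 5.3 | Content and length |
| Exclusion of too sensitive material | 5.3 | Content |

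One of the six masks the speaker. For someone recorded in audio only, blurring has nothing to act on.

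**4. Who sees the film?** Section 5.3 gives 4 young people + 4 carers + 4 professionals = 12 participants. With 3 researchers and the principal investigator, 12 + 3 + 1 = 16 people are in the room. The team already has access to the data, so the added audience is 12. Section 5.3.1 schedules the viewing in the first workshop.

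**5. Could a viewer know the speaker?** Workshop members register through the study's consent form (5.3), so they come from the same participants. Recruitment runs through four Trusts (5.4), with local clinicians identifying and inviting young people (5.5). Interviews may be held in the young person's own service (5.2). Nothing in the article excludes a speaker's own carer or clinician from the audience. It is a possibility that the text leaves open, not a planned event.

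**6. Withdrawal.** Read literally, the phrase in 5.8 sets no end date. The likely intention is a right to withdraw during data collection and for four weeks afterwards. The timing matters because a clip cannot be recalled once it has been shown.

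**The case against.** The strongest reply is that the plan is open about the film and surrounds it with checks. Participants are told in advance, film use is only a possibility, they can object, concerns are invited after recording, and segments are reviewed. The leaflet and consent form are not shown, ethics approval was obtained, and separate consent may already be in those papers. All of this is fair, and the fault is incomplete mitigation of a risk that the protocol recognises. Unseen papers would not, however, remove the conflict between 5.1 and 5.2 or the absolute promise as printed.

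The promise can also be read as a commitment additional to blurring. In that case the article still names no other means of keeping it.

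Four stronger readings are tempting and are not supported:

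- **That 5.8 flatly contradicts 5.2 by making recording compulsory.** The same list in 5.8 includes the workshops ("for the interviews/focus groups to be recorded, and for the four" follow-up workshops), which are plainly voluntary under 5.1 and 5.3. The list is better read as requiring consent for each element. The real conflict lies with 5.1 and 5.7.
- **That all 45 planned participants (15 + 15 + 15) are recorded and shown to 16 people at every workshop.** The number recorded is unknown if recording is a choice. There is one film, and its viewing is scheduled once.
- **That the film keeps voices unaltered.** The article does not say how voices are handled, and quotes might be shown as text.
- **That accounts will be biased towards milder criticism of services.** Section 5.2 raises an effect on disclosure without giving a direction, and nothing in the document establishes one.

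**Conclusion.** The concern holds in a limited form. As written, the plan ties possible film use to a recording that the analysis depends on, and it promises non-identification with one picture-only masking step. It would not reliably keep that promise before 12 viewers outside the team. The effect on candour is a risk that the protocol itself names; its size and direction cannot be estimated from the documents. No numerical result changes. The withdrawal phrase is a wording correction.

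The conclusion assumes that clips may carry the speaker's voice or a recognisable account, and that some viewers may know some speakers. Both are plausible from the text, and neither is stated. If the full consent papers already separate film use and provide for masking of audio and identifying details, what remains is to align the printed sections and correct the withdrawal wording. The change is worth making before filming, because it cannot protect anyone after a clip has been shown.

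**What to change.** 1. Obtain two consents: one for recording for transcription and analysis, and a separate opt-in for film use, confirmed after the interview when the participant knows what was said.
2. Mask or re-voice the audio and remove identifying details from the clips. Otherwise, replace the absolute promise with a statement that steps will be taken to prevent identification.
3. Align sections 5.1, 5.2, 5.7 and 5.8 on whether recording is required. If it is optional, say how an unrecorded interview enters the analysis.
4. Restate withdrawal as possible during data collection and up to 4 weeks after it, say whether this runs from each participant's own session, and finalise the film only after that date.

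The cost is an amendment to the consent form and leaflet, simple audio editing, some loss of authenticity in the film, a few refused clips, and a possible short wait before the first workshop.
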